### Sample Size

To conduct a repeated measures analysis of variance (ANOVA) with 4 time points (ie, T1, T2, T4, and T5) for self-reported child anxiety, Cohen *f* of 0.25, an alpha of .05 (2-tailed), and a power of .85, a sample size of 200 patients is needed (100 patients per group). To perform regression analyses with 6 predictor variables, a small to medium effect size, and a power of .85, a sample size of 100 patients in the intervention group is sufficient.

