### Patient Recruitment and Procedure

Eligible patients and their parents will be informed about the study by phone and, if interested, receive the patient information folder (PIF) by email. Participation will be voluntary and all data will be anonymized. Both parents will be asked to provide written informed consent. Patients who are 12 years old will also be asked to provide written informed consent themselves. Children under 12 years old will give their permission orally.

After informed consent is provided, children will be randomly allocated to the VRE intervention (N=100) or CAU (N=100) group at hospital admission. Randomization will be stratified by age group (4- to 7- or 8- to 12-years-old), and type of surgery (ie, oral and maxillofacial surgeries, tonsil and adenoidectomy, tympanostomy tubes, or other ear surgeries). The researchers and operating staff will be blinded to group allocation. The research assistant will not be blinded, since he/she will be guiding the intervention. This will take place in a separate room, in the presence of an accompanying parent. Un-blinding takes place if patients are excluded from the study and after the final assessment of the last included patient.

Assessments will be carried out at the following time points: (1) T1, admission to the hospital, before possible intervention; (2) T2, after the VRE intervention or after CAU, in the holding area; (3) T3, during induction of anesthesia, in the operating room; (4) T4, postoperatively, in the recovery room; and (5) T5, 3 days after surgery, at home.

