**Figure 5 figure5:**
[figure not shown]
Flow chart of the study design with outcomes, instruments, and informants at each time point.

For the secondary outcome measures, repeated measures ANOVA will be conducted with situational parental anxiety at T1 and T3 as within variables and group as between variables. Also, repeated measures ANOVAs will be performed using postoperative pain at T4 (in the recovery room) and T5 (at home) as outcomes, with group as between variables. The effect of the intervention on emergence delirium at T4 will be examined with an analysis of covariance (ANCOVA). Age and sex effects will be accounted for in all analysis.

Multiple linear regression analyses will be performed with change in child state anxiety between T1 and T3 and change in pain between T4 and T5 as outcomes. Predictor variables (ie, socioeconomic status, age, sex, type of surgery, preoperative child, and preoperative parental trait anxiety) will be included into the linear models to identify which factors influence VRE efficacy.

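### The 85% power claimed for the six-predictor regression in 100 children is not reached by the overall model test, holds only for single predictors in the upper part of the small-to-medium range, and concerns slopes that cannot show which factors influence VRE efficacy

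*Protocol article*

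**What the plan says.** The Sample Size section has two sentences. The first derives the total of 200 from a repeated measures ANOVA at "an alpha of .05 (2-tailed), and a power of .85, a sample size of 200 patients is needed". The second covers the predictor analyses: "To perform regression analyses with 6 predictor variables, a small to medium effect size, and a power of .85", for which "a sample size of 100 patients in the intervention group is sufficient". The only description of the effect is "a small to medium effect size". There is no f2 or R2, no statement of whether the power refers to the whole model or to one coefficient, and no alpha in that sentence.

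The Statistical Analyses section describes the model. The outcomes are change in child state anxiety from T1 to T3 and change in pain from T4 to T5. On the predictors it says: "Predictor variables (ie, socioeconomic status, age, sex, type of surgery, preoperative child, and preoperative parental trait anxiety) will be included" in the linear models, with the aim "to identify which factors influence VRE efficacy". Treatment group is not among the predictors listed.

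The randomization paragraph under Patient Recruitment and Procedure gives the categories of type of surgery: "oral and maxillofacial surgeries, tonsil and adenoidectomy, tympanostomy tubes, or other ear surgeries".

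**The concern.** A sufficiency claim that combines a number of predictors, an effect size and a power looks like a calculation for the overall regression test. On that test, 100 children appear too few for any effect up to medium. One of the six predictors also has four categories, so six variables need not mean six parameters.

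There is a second problem. The calculation is for the intervention group alone, while the question is what influences the efficacy of VRE. Efficacy in this trial is a contrast of VRE with care as usual, and a regression in one arm contains no such contrast.

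What is at stake is interpretation. A reader who takes 85% as assurance may read a non-significant predictor as having no influence on VRE efficacy, or a significant one as a modifier of the VRE effect. Neither conclusion would be supported.

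**Working it through.** **Inputs from the Protocol article**
- n = 100 (intervention group), 6 predictors, power .85: Sample Size.
- Six named variables: Statistical Analyses.
- Four surgery categories: Patient Recruitment and Procedure. Dummy coded, they take 3 df, so the model has 5 + 3 = 8 df.

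**Assumptions not in the article**
- Alpha .05 two-sided, carried over from the ANOVA sentence.
- Small f2 = .02 and medium f2 = .15.
- Surgery type coded with the four stratification categories, for the 8-df figures only.

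**Formula.** Power = P(F′ > F crit), where F′ is noncentral F with u and v = n − p − 1 df and noncentrality λ = f2 × n. Here u is the df of the test and p the df of the model.

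**1. Trying to reproduce 100.**
- Overall test, u = p = 6: no f2 up to .15 gives n = 100. At f2 = .15 the n for 85% is 109.
- Single coefficient, u = 1, p = 6: f2 = .09 needs n = 102 and gives power .844 at n = 100. At f2 = .0917, λ = .0917 × 100 = 9.17, v = 93, F crit = 3.94 and power is .850.

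The stated 100 can therefore be matched, but only on the single-coefficient reading and at an f2 of about .09 that the article does not state.

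**2. Overall model test at n = 100.** At f2 = .15, λ = .15 × 100 = 15. With 6 df, v = 93 and F crit = 2.20; with 8 df, v = 91 and F crit = 2.04.

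| f2 | Power, 6 df | Power, 8 df |
|---|---|---|
| .02 | .139 | .124 |
| .05 | .315 | .273 |
| .085 (midpoint of .02 and .15) | .528 | .466 |
| .10 | .609 | .545 |
| .15 | .813 | .758 |
| f2 needed for .85 | .163 | .182 |

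The n for 85% at f2 = .15 is 109 (6 df) or 120 (8 df). At f2 = .085 it is 186 or 206.

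**3. Tests of individual predictors at n = 100.**

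| f2 | 1-df coefficient (p = 6) | 3-df surgery type (p = 8) |
|---|---|---|
| .02 | .288 | .186 |
| .05 | .600 | .424 |
| .085 | .823 | .663 |
| .092 | .851 | .701 |
| .15 | .969 | .904 |
| f2 needed for .85 | .092 | .128 |

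Using 8 rather than 6 model df leaves the 1-df requirement at .092.

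**4. The question about efficacy.** Write the slope of a factor on anxiety change as b(VRE) in one arm and b(CAU) in the other. The factor influences efficacy if b(VRE) − b(CAU) differs from zero. A regression in the VRE arm estimates b(VRE) only. If b(VRE) = b(CAU), the factor predicts anxiety change equally under both kinds of care and does not alter the VRE effect, yet the test of b(VRE) can still be significant.

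For scale, assume that the slope difference equals the slope detectable at 85% in one arm (f2 = .0917), with equal arms and equal variances. The variance of a difference of two independent slopes is twice that of one slope, so λ halves: 9.17 / 2 = 4.585. With 1 df, F crit = 3.89 (error df about 185) and power is .57 in all 200 children.

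**The case against.** The strongest reply is that the article never says the power is for the overall test. Its stated aim is to identify factors, which points to individual coefficients. On that standard reading 100 children give 85% power at f2 of about .092, which lies between small and medium. The surgery-type test also reaches 85% inside the range, at about .128. This stands. A reader might infer from the overall-test figures that the sentence is simply wrong, but the article does not support that inference because it names no test.

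It is also fair that the 8-df model is an inference. The four categories come from the randomization strata, and the coding of the regression may be fixed in an analysis plan that is not shown. With 6 df the gap at a medium effect is modest: 81% against 85%, or 109 children against 100. The larger shortfalls depend on effect sizes chosen here within a range the article does not quantify.

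A further reply is that effect modification is a design question rather than an arithmetic one, and that 57% is the power of an analysis not planned. That is correct, and the figure is not evidence against the printed calculation. The mismatch itself remains: the article states both the arm in which the regression is powered and the question it is meant to answer, and the two do not fit.

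The reply does not rescue the sentence as printed. The claim is made for small-to-medium effects without limit, and even the favourable reading fails in the lower part of that range (60% at f2 = .05, 29% at .02).

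**Conclusion.** The point holds in limited form.

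- **Overall model test:** the stated .85 is not reached anywhere in the assumed small-to-medium range. The best case is 81% (6 df) or 76% (8 df), at f2 = .15.
- **Individual predictors:** it is reached from f2 of about .092 (1 df) or .128 (3-df surgery type) upward, and not below.
- **Aim:** within-arm slopes do not answer which factors influence VRE efficacy, whatever their power.

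The first two results rest on alpha .05 and the benchmarks .02 and .15; the 8-df and 3-df figures also rest on four-category coding of surgery type. The third needs no numerical assumption.

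This is a secondary predictor analysis. A reader might infer that the trial as a whole is too small, but the total of 200 is derived from the ANOVA sentence and nothing here bears on it. A correction of wording and analysis labelling is proportionate.

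**What to change.** Replace the regression sentence with one that names the test, f2, df and alpha. For example: 100 children give about 85% power for a single 1-df coefficient at f2 of about .09, and about 81% (6 df) or 76% (8 df, surgery type in four categories) for the overall model at f2 = .15.

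In Statistical Analyses, assess influence on VRE efficacy with group-by-factor interactions in all 200 children. Note that power is about 57% if the slope difference equals the slope detectable at 85% in one arm, and mark that as an assumption. Describe any regression within the VRE arm as identifying predictors of anxiety or pain change in children who received VRE.

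Label all of these analyses exploratory, and report estimates with confidence intervals so that a non-significant factor is not read as having no influence.

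The cost is a less favourable stated figure and a little more analysis. No extra patients are needed and the trial size stays at 200.

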### Outcome Measures

An overview of the study design and variables at each time point are provided in Figure 5. The primary outcome is change in child state anxiety level between baseline (T1) and induction of anesthesia (T3), evaluated by a psychologist trained in the administration of the modified Yale Preoperative Anxiety Scale (mYPAS) [20,21]. The mYPAS is a commonly used observational tool consisting of 27 items divided into 5 domains: activity, emotional expressivity, state of arousal, vocalization, and use of parents.

Multiple secondary state anxiety outcomes will be examined. Children will indicate their level of anxiety with a Visual Analogue Scale (VAS) at different time points (T1, T2, T4, and T5) [22]. Moreover, situational parental anxiety, both pre- and postoperatively will be self-reported using the state anxiety form (20 items) of the State-Trait Anxiety Inventory (STAI) at T1 and T3 [23,24]. Either the psychologist (T1 to T3) or the recovery nurse (T4) will assess parental anxiety with the VAS.

Postoperative pain will be reported with 3 different instruments. The revised Faces Pain Scale (FPS-r) is a self-report measure designed for children to indicate pain intensity [25]. This measure will be used at T4 and T5. A recovery nurse, trained in administering the Face, Legs, Activity, Cry, and Consolability (FLACC) scale, will assess pain intensity at T4 [26,27]. This scale assesses nonverbal indicators of pain. The Parents’ Postoperative Pain Measure (PPPM) will be completed by parents at T5 [28].

Emergence delirium will be measured with the Pediatric Anesthesia Emergency Delirium (PAED) scale by the recovery nurse at T4 [29,30]. Finally, information regarding use of analgesics and healthcare use will be extracted from medical records.

Several factors associated with situational anxiety will be assessed because these may influence the efficacy of the VRE. Putative predictors are socioeconomic status, age, sex, type of surgery, preoperative child, and parental trait anxiety. Child trait anxiety will be assessed by parents with the Child Behavior Checklist (CBCL) at T1 [31]. Parental trait anxiety will be self-reported using the trait anxiety form (20 items) of the STAI.

### Statistical Analyses

To examine the effect of the intervention on the primary outcome, a repeated measures ANOVA will be conducted with child state anxiety level at T1 (baseline state anxiety) and T3 (anxiety during induction of anesthesia) as within variables and group (VRE versus CAU) as between variables.

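### The primary ANOVA uses baseline mYPAS as an outcome level rather than a covariate: valid, but in large samples never more precise than ANCOVA of T3 on T1

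*Protocol article*

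**What the plan says.** Under Outcome Measures, the protocol article states: "The primary outcome is change in child state anxiety level between baseline (T1) and induction of anesthesia (T3"), rated on the mYPAS. Under Statistical Analyses, the model is a repeated measures ANOVA with "child state anxiety level at T1 (baseline state anxiety) and T3 (anxiety during induction of anesthesia) as within variables". Treatment arm, VRE or CAU, is the between factor. Patient Recruitment and Procedure describes the first assessment as "T1, admission to the hospital, before possible intervention".

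The only covariate adjustment stated for this model is in the Statistical Analyses text after Figure 5: "Age and sex effects will be accounted for in all analysis". Baseline mYPAS is not a covariate. ANCOVA is named only for emergence delirium. The parental outcome has the same structure as the primary one: "repeated measures ANOVA will be conducted with situational parental anxiety at T1 and T3 as within variables".

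The article does not say in words which term of the ANOVA tests efficacy. The outcome is defined as change, and group-by-time is the term that compares change between groups.

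**The concern.** T1 cannot be affected by the intervention, so the expected group difference there is zero. Treating T1 as a second outcome level forces the analysis to subtract the whole baseline score from the T3 score. ANCOVA subtracts only as much of it as predicts T3. When r is modest, subtracting all of it adds noise to the comparison.

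What is at stake is precision on the primary endpoint, in a trial that already collects everything needed to recover it. The stated sample size offers no demonstrated margin for this test, because it was calculated "with 4 time points (ie, T1, T2, T4, and T5) for self-reported child anxiety" and not for mYPAS at T1 and T3.

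**Working it through.** **Inputs from the document.** 100 children per group; primary outcome mYPAS change from T1 to T3; T1 before the intervention; adjustment for age and sex.

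**Assumed, because the document gives no values.** The T1-T3 correlation r (0.2 to 0.7), the ratio of the T3 SD to the T1 SD (1, 1.5 or 2), and a true group difference of 0.5 T3-SD at T3. Cohen f = 0.25 in the Sample Size section belongs to self-reported anxiety at four time points and does not supply an mYPAS effect.

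**The plan's own figure.** For a group-by-time test with 2 groups and 4 time points, take noncentrality f²N = 0.25² × 200 = 12.5 with 3 and 3 × 198 = 594 degrees of freedom. Power is 0.854, so N = 200 reproduces. It concerns a different outcome and is not disputed here.

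**Step 1: what the planned test is.** With two time points, the group-by-time F is the square of the two-sample t on D = T3 − T1. Per-patient variances, leaving age and sex aside, are:

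- Change score: SD_T1² + SD_T3² − 2·r·SD_T1·SD_T3
- ANCOVA of T3 on T1: SD_T3²·(1 − r²)
- Excess of change over ANCOVA: SD_T1² − 2·r·SD_T1·SD_T3 + r²·SD_T3² = (SD_T1 − r·SD_T3)²

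The excess is never negative. It is zero when SD_T1 = r·SD_T3, that is, when the slope of T3 on T1 equals 1.

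**Step 2: equal SDs (both 1).** The ratio of ANCOVA to change variance is (1 − r²)/[2(1 − r)] = (1 + r)/2. Power is from the two-sample t test, 100 per arm, two-sided 0.05, difference 0.5.

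| r | Change variance | ANCOVA variance | Ratio | Power, change | Power, ANCOVA |
|---|---|---|---|---|---|
| 0.2 | 1.60 | 0.96 | 0.60 | 79% | 95% |
| 0.3 | 1.40 | 0.91 | 0.65 | 84% | 96% |
| 0.5 | 1.00 | 0.75 | 0.75 | 94% | 98% |
| 0.7 | 0.60 | 0.51 | 0.85 | 99.5% | 99.8% |

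A simulation (4,000 runs) at an assumed difference of 0.4 SD gave change versus ANCOVA power of 0.67 vs 0.84, 0.80 vs 0.90 and 0.95 vs 0.98 at r = 0.3, 0.5 and 0.7. The formulas give 0.67 vs 0.84, 0.81 vs 0.90 and 0.96 vs 0.98.

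**Step 3: T3 SD 1.5 times the T1 SD** (SD_T1 = 1, SD_T3 = 1.5, difference 0.5 × 1.5 = 0.75).

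| r | Change variance | ANCOVA variance | Ratio | Power, change | Power, ANCOVA |
|---|---|---|---|---|---|
| 0.2 | 2.65 | 2.16 | 0.82 | 90% | 95% |
| 0.3 | 2.35 | 2.05 | 0.87 | 93% | 96% |
| 0.5 | 1.75 | 1.69 | 0.96 | 97.9% | 98.2% |
| 0.7 | 1.15 | 1.15 | 1.00 | 99.8% | 99.8% |

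With a T3 SD twice the T1 SD and r = 0.5, the excess is (1 − 0.5 × 2)² = 0 and ANCOVA gains nothing.

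**Step 4: the group main effect.** It compares the mean of T1 and T3, so it estimates (0 + δ)/2, half the T3 effect δ. With equal SDs its variance is (1 + r)/2. For δ = 0.5 its power is 62%, 59% and 53% at r = 0.2, 0.3 and 0.5.

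**The case against.** The strongest defence is that the model matches the outcome as defined. The outcome is change, the group-by-time term tests change, and under randomisation that test is unbiased with the correct type I error. This stands. A reader might infer that the primary analysis is biased, for example because a chance imbalance at T1 carries over through regression to the mean. That is a bias conditional on an observed imbalance. Over repeated randomisation there is none, so the point concerns efficiency and not validity.

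A reader might also infer that the diluted group main effect will be reported as the efficacy result. The document does not support this. Nothing proposes that term as the test, and defining the outcome as change points to the interaction. Naming the model term is also detail that an article can leave to the full protocol or analysis plan.

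Third, the contrast of 79% with 95% needs equal SDs, r = 0.2 and a 0.5 SD effect, none of which is in the document. Admission and induction are very different situations, so equal SDs cannot be taken for granted. This also stands, and the gain must be given as a range that reaches zero. In small samples, when the slope of T3 on T1 is close to 1, ANCOVA gains nothing and gives up one degree of freedom; with 200 children that cost is negligible.

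The defence does not remove the point that the article itself names the model and its adjustment. The criticism is of a stated choice, not of missing detail.

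**Conclusion.** The point holds as one of efficiency. The planned primary test is valid, but it handles a pre-intervention score in a way that in large samples cannot be more precise than baseline adjustment and may be clearly less precise. With equal SDs, ANCOVA variance is 15% to 40% lower for r between 0.7 and 0.2. With a T3 SD 1.5 times the T1 SD, it is between about 0% and 18% lower. Both r and the SDs are assumptions, so the document does not show where in this range the trial lies. The planned age and sex terms do not in general recover the loss, because they do not stand in for the baseline score. The stated N of 200 is not refuted by this point. The group main effect should not be read as the efficacy test, although the plan does not propose it as one.

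**What to change.** Make the primary analysis a linear model of T3 mYPAS on group, adjusted for T1 mYPAS, age, sex and the stratification factors (age group and type of surgery). Keep the planned age adjustment alongside the age stratum rather than letting the two-level stratum replace it. Report the adjusted VRE-minus-CAU difference at T3 with its 95% CI as the single primary test. Keep the group-by-time interaction as a sensitivity analysis, and state that the group main effect is not an efficacy test. Use the same form for parental STAI, with T3 as outcome and T1 as covariate.

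The cost is a change of wording, made before allocation is unblinded. T1 and T3 are already collected, so no new data or patients are needed.

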**Figure 5 figure5:**
[figure not shown]
Flow chart of the study design with outcomes, instruments, and informants at each time point.

For the secondary outcome measures, repeated measures ANOVA will be conducted with situational parental anxiety at T1 and T3 as within variables and group as between variables. Also, repeated measures ANOVAs will be performed using postoperative pain at T4 (in the recovery room) and T5 (at home) as outcomes, with group as between variables. The effect of the intervention on emergence delirium at T4 will be examined with an analysis of covariance (ANCOVA). Age and sex effects will be accounted for in all analysis.

Multiple linear regression analyses will be performed with change in child state anxiety between T1 and T3 and change in pain between T4 and T5 as outcomes. Predictor variables (ie, socioeconomic status, age, sex, type of surgery, preoperative child, and preoperative parental trait anxiety) will be included into the linear models to identify which factors influence VRE efficacy.

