## Introduction

Fifty to 70% of children experience elevated levels of anxiety and distress prior to surgery [1,2]. Preoperatively, anxious children are more often agitated, sad, emotional, less cooperative, and more resistant compared to children who are not anxious [3,4]. Preoperative anxiety is also associated with a higher incidence of emergence delirium, more intense and prolonged pain postoperatively, and poorer recovery [3,5,6]. A child’s operation is also a stressful experience for parents and parental fear has been shown to intensify children’s preoperative anxiety [7,8]. Anxious children undergoing surgery, as well as their parents, are even at risk for a posttraumatic stress disorder [9]. These adverse outcomes underscore the urgent need to develop effective strategies to minimize preoperative anxiety in children.

Education programs have proven to be effective in reducing children’s preoperative anxiety. Nonetheless, a recent systematic review by Copanitsanou and Valkeapää indicated that education seems to have a negative effect on younger children’s anxiety [10]. Other complementary methods for reducing preoperative anxiety in children predominantly focus on distraction, for instance, watching a video, listening to music, playing video games, or distraction by clowns [11-14]. However, scientific literature shows that gradual exposure is a much more effective way to reduce anxiety in children than mere distraction [15]. Due to busy clinical practices and the daily use of surgery rooms, exposing children to all pre- and postoperative aspects is often not feasible.

Virtual reality exposure (VRE) offers the possibility to expose children of different ages to a highly realistic virtual environment that mimics the operating theater of a hospital. Children can get accustomed not only to the operating environment, but also to the procedures associated with anesthesia. VRE has already been shown to be effective as a treatment for specific phobias in children, such as a fear of heights or a fear of flying [16]. To the best of our knowledge, the efficacy of VRE to prepare children for general anesthesia and surgery has not yet been studied. Furthermore, Cochrane reviews showed that most studies examining interventions for induction of anesthesia in children are small and of poor quality [17,18]. As such, high-quality randomized controlled trials (RCTs) are needed.

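### Emergence delirium ANCOVA: age and sex are the only covariates named, and prespecifying T1 child anxiety would be a nearly free, probably modest, gain in precision

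*Protocol article*

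**What the plan says.** The Statistical Analyses section gives the delirium model in one sentence: "The effect of the intervention on emergence delirium at T4 will be examined with an analysis of covariance (ANCOVA"). That sentence lists no covariates. The next one applies to all models: "Age and sex effects will be accounted for in all analysis". No other adjustment is named for delirium.

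Under Outcome Measures, "Emergence delirium will be measured with the Pediatric Anesthesia Emergency Delirium (PAED) scale by the recovery nurse at T4", and at no other time. Pain is analysed by repeated measures ANOVA on T4 and T5, so it has no preoperative value in the model either.

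Child anxiety is available earlier. "The primary outcome is change in child state anxiety level between baseline (T1) and induction of anesthesia (T3"), rated with the mYPAS, so a T1 score is planned. Self-reported anxiety on a VAS is also collected at T1. Patient Recruitment and Procedure defines the first assessment as "T1, admission to the hospital, before possible intervention".

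The Introduction gives the reason to expect a link: "Preoperative anxiety is also associated with a higher incidence of emergence delirium, more intense and prolonged pain postoperatively, and poorer recovery".

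**The concern.** The models for child anxiety and parental anxiety both use a T1 value of the outcome. The delirium and pain models cannot, because these outcomes do not exist before surgery. In that situation one looks for a baseline variable that predicts the outcome and is unaffected by treatment. The article points to a candidate (preoperative anxiety), collects it before the intervention, and does not name it in the models for the outcomes it is said to be associated with.

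What is at stake is precision. If T1 anxiety predicts PAED beyond age and sex, the residual variance is larger than it needs to be, and the confidence interval for the delirium difference is correspondingly wider. A chance difference between arms in T1 anxiety would also shift the delirium estimate a little, in proportion to the correlation.

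**Working it through.** **Inputs from the article.** 200 children, 100 per arm (Sample Size); covariates named: age and sex (Statistical Analyses); PAED at T4 only, mYPAS at T1 and T3 (Outcome Measures); T1 before the intervention (Patient Recruitment and Procedure).

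**Inputs not in the article.** The correlation r between T1 mYPAS and PAED, partial on age and sex; the SD of PAED; a target difference for PAED. I assume r = 0.2, 0.3 and 0.4 and, for illustration, a difference of 0.4 SD. Both are assumptions.

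**The plan's own figure.** The stated N of 200 can be reproduced with a noncentral F test: λ = N·f² = 200 × 0.25² = 12.5, df1 = 4 − 1 = 3, df2 = 3 × (200 − 2) = 594, giving power 0.854 against the stated 0.85. That calculation is for self-reported child anxiety over four time points. No power is stated for delirium, so the delirium analysis has no planned figure to compare with.

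**Effect of adding T1 mYPAS to the PAED model.**
- Residual variance is multiplied by 1 − r².
- Confidence interval width is multiplied by √(1 − r²).
- Equivalent N without the covariate is 200 / (1 − r²).
- Power is from the noncentral t with 100 per arm, two-sided 0.05, at a standardized difference of 0.4 / √(1 − r²).

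| r (assumed) | 1 − r² | CI narrower by | Equivalent N | Power at 0.4 SD |
|---|---|---|---|---|
| 0 | 1.00 | 0% | 200 | 0.804 |
| 0.2 | 0.96 | 2.0% | 200/0.96 ≈ 208 | 0.819 |
| 0.3 | 0.91 | 4.6% | 200/0.91 ≈ 220 | 0.839 |
| 0.4 | 0.84 | 8.3% | 200/0.84 ≈ 238 | 0.867 |

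The last column depends on the assumed 0.4 SD as well as on r. The other columns depend on r alone.

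**Cost if r is zero.** With intercept, group, age and sex, the residual degrees of freedom are 200 − 4 = 196. The extra covariate makes it 195.

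**Chance imbalance.** The SD of the between-arm difference in a standardized baseline variable is √(2/100) = 0.14. At r = 0.3 a typical imbalance moves the unadjusted PAED difference by 0.3 × 0.14 ≈ 0.04 SD. An imbalance at the 95% limit, 1.96 × 0.14 ≈ 0.28 SD, moves it by about 0.08 SD.

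**Pain.** These figures apply to one outcome at one time point. In a repeated measures model over T4 and T5, a T1 covariate acts mainly on the between-group effect. The group-by-time effect is tested against within-child error, which the covariate need not reduce. No gain has been calculated for pain.

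**The case against.** The strongest objection is that nothing here is an error. The sentence on age and sex may be a minimum for every model, not a closed list. The article is condensed, and the full protocol or analysis plan may already name further covariates. This stands. A reader might infer that delirium is adjusted for age and sex and nothing else; the article supports only that nothing else is named.

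A reader might also infer that omitting anxiety biases the delirium comparison, or that any baseline imbalance passes straight into it. Neither follows. Randomization makes the comparison unbiased, imbalance carries over only in proportion to r, and the unadjusted standard error already allows for it.

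Third, the Introduction speaks of preoperative anxiety in general. It does not say that anxiety at admission predicts delirium. The association could run mainly through anxiety in the holding area or at induction (T2, T3). Those values follow randomization and may be changed by the intervention, so they are unsuitable as covariates. This also stands, and it is a reason to take the low end of the range for r seriously.

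Finally, no correlation, SD or target difference for PAED is given, and any part of the anxiety–delirium association shared with age is already captured by adjusting for age. The size of the gain therefore cannot be established from the article.

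What remains after all four is that T1 mYPAS is collected anyway, is a legitimate baseline covariate with a stated rationale, and costs almost nothing to include.

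**Conclusion.** The point holds as an optional improvement to secondary analyses. The delirium comparison is valid and unbiased as planned, and the article contains no contradiction here. Naming T1 mYPAS as a covariate would use information already collected to gain some precision. For PAED the gain equals about 8, 20 or 38 extra children on top of 200 at an assumed partial r of 0.2, 0.3 or 0.4. That is negligible at 0.2 or below and modest above. Nothing in the article shows which value applies. For pain the direction is the same for the between-group effect, but its size is not established.

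**What to change.** State that the ANCOVA for PAED at T4 includes T1 mYPAS as a covariate alongside age and sex. Add the same covariate for the between-group effect in the T4/T5 pain models. Specify T1 only, and say that T2 and T3 anxiety are excluded because they follow randomization and may be affected by the intervention. If the full protocol or analysis plan already names T1 mYPAS in these models, confirming that is enough.

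The wording should be fixed before the unblinding that the article places after the last child's final assessment, so that the choice of covariate cannot be seen as driven by the data. The cost is a change of wording and one degree of freedom per model; no new data are needed.
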